### Potential confounders and effect modifiers

We will collect information on both time-variant and time-invariant factors considering the multiple study designs. Race/ethnicity is controlled for in the self-control analysis but will be a possible confounder in the cohort analysis. While season does appear to be associated with Kawasaki disease,[^19^](#_ENREF_19) we do not expect it to be associated with vaccination status or timing. Viral and bacterial illnesses have been suggested as possible etiological agents of Kawasaki disease. ^24,29^ When available in the medical chart, we will capture information on infections occurring in the 60 days prior to onset of Kawasaki disease. Additionally, PCV13 is generally given concomitantly with multiple other vaccines and this can be a source of confounding.

### Statistical power

One-sided power calculations were done for the self-controlled risk interval analysis, alpha=0.05, and all PCV13 doses. PCV13 dose counts were obtained from four Data Partners in March, 2015. Background rates of ICD-9 code identified Kawasaki disease were estimated by counts in three Data Partners as we expect that background rates would be consistent among the Data Partners. The results of the self-controlled risk interval power calculations, assuming all potential cases are chart confirmed, are shown in Table 2 below. There will be 80% power to detect a relative risk of 1.9.

Table 2. Power calculation based on a total 3,388,104 PCV13 doses

| **Power calculation for the self-controlled risk interval design** | | |
| --- | --- | --- |
| Kawasaki disease diagnosis/100,000 Person Years | Relative Risk | Power |
| 8.7 | 1.1 | 9.3 |
| 8.7 | 1.2 | 15.5 |
| 8.7 | 1.3 | 23.6 |
| 8.7 | 1.4 | 33.1 |
| 8.7 | 1.5 | 43.5 |
| 8.7 | 1.6 | 53.8 |
| 8.7 | 1.8 | 72.3 |
| 8.7 | 1.9 | 80.0 |
| 8.7 | 2.0 | 85.5 |
| 8.7 | 2.1 | 90.0 |
| 8.7 | 2.5 | 98.3 |
| 8.7 | 3.0 | 99.9 |
| 8.7 | 4.0 | 100.0 |
| 8.7 | 5.0 | 100.0 |

If we assume 80% chart retrieval and 50% chart confirmation (0.4 overall, or 3.5 confirmed cases/100,000 person-years), based in part on past experience with chart-review studies in PRISM, the relative risk that could be detected with 80% power would be between 2.5 and 3.0, as shown in Table 3.

Table 3. Power calculation based on the above but assuming only 40% of the potential cases are ultimately confirmed.

| **Power calculation for the self-controlled risk interval design (0.4 of confirmed cases in Table 2)** | | |
| --- | --- | --- |
| Kawasaki disease diagnosis/100,000 Person Years | Relative Risk | Power |
| 3.5 | 1.1 | 7.5 |
| 3.5 | 1.2 | 10.7 |
| 3.5 | 1.3 | 14.5 |
| 3.5 | 1.4 | 19.0 |
| 3.5 | 1.5 | 24.0 |
| 3.5 | 1.6 | 29.4 |
| 3.5 | 1.8 | 41.0 |
| 3.5 | 1.9 | 47.3 |
| 3.5 | 2.0 | 52.7 |
| 3.5 | 2.1 | 58.3 |
| 3.5 | 2.5 | 76.8 |
| 3.5 | 3.0 | 90.7 |
| 3.5 | 4.0 | 99.0 |
| 3.5 | 5.0 | 99.9 |

### Evaluation of Elevated Risks

If a statistically significant elevated risk is found in any of the analyses, we will perform the following:

1. Check data quality, descriptive statistics and background rates by age, sex and Data Partner.
2. Use the temporal scan statistic to test for temporal clustering of chart-confirmed Kawasaki disease cases in the weeks after the dose in question.

### Automated code analysis

As an exploratory objective, if the positive predictive value of the ICD-9 code 446.1 and ICD-10 code M30.3 (acute febrile mucocutaneous lymph node syndrome) in the inpatient setting is ≥0.8 for Kawasaki disease among the chart confirmed cases, we will report the automated code analyses in addition to the chart reviewed analyses. For the automated code analyses, we will estimate day of symptom onset based on the median number of days from onset to diagnosis for the cases that are chart reviewed.

## Medical Chart Review

Medical records of all cases of inpatient diagnosis of Kawasaki disease, limited to the first inpatient diagnosis in 365 days, occurring during eligible person-time in the study period will be reviewed, regardless of vaccination status or timing relative to vaccination. The maximum total number of cases to be reviewed is 200 among all Data Partners combined. If the available number of cases exceeds 200, we will use a pre-specified sampling scheme to ensure that the highest-priority cases are reviewed. Top priority cases are those that fall within either the risk or control window of the self-control designs. All of these will be chart reviewed. High priority cases include the remaining cases falling between 0 and 18 months of age and during the period of time when PCV13 was administered, starting from the most recent time period and moving back in time. A chart abstraction form will be used.

In order to identify the cases and obtain the medical charts, we will send programs for the Data Partners to run on their uniform-format patient-level files. These programs will produce a report of the number and characteristics (e.g., age and sex) of the cases and, for each case, a report listing the healthcare encounters occurring within a specified number of days of the Kawasaki disease diagnosis, to be specified after the first review of the descriptive characteristics. The reports will include information on clinical setting, actual diagnosis, and date of the diagnosis.

Next, PRISM clinical investigators will rank the encounters of each case using relevant diagnosis and procedure codes provided in the report to identify those that seem likely to produce the most definitive diagnostic information. The ranked list will be returned to the Data Partners who will then attach patient name, insurance member number, and provider name and address to all visits. Another PRISM program to be run at the Data Partners will organize the list of charts to pull by facility.

Each Data Partner will identify a preferred vendor to create chart extracts. These chart extracts will consist of components pre-specified by the PRISM team that need to be photocopied or scanned by the vendor. Examples of such items include the admission note, the daily notes during hospitalization, the discharge summary, all cardiology reports within 12 weeks of the index date (defined as the first day of fever or the date of the first code for Kawasaki disease if the first date of fever is missing) and all diagnostic procedures, such as echocardiograms and angiograms. Using the list provided by the Data Partner, the chart-review vendor will notify the facilities, contact them to obtain the charts, photocopy or scan the appropriate pages of the chart, and redact the record of all personal identifiers. The Data Partners will have the option of reviewing the redacted records to ensure that the redaction is complete. The redacted records will be sent to the Sentinel Operations Center for further review and abstraction by the PRISM team.

All investigators classifying the cases will be blinded to vaccination status. PRISM clinical investigators will review the chart abstractions and classify the cases. Two clinical investigators will independently review 10 charts, blinded to vaccination history as well as to the other reviewer’s decision. This initial round of case classification will enable refinement of the classification rules. Using the refined set of rules, investigators will complete a second round of case classification for another 10 cases. If there are zero discrepancies between reviewers after the second round, then the review will continue to use a single reviewer for the remainder of the cases. If there are any discrepancies regarding the 10 second-round cases, double review of each subsequent case will be required with regular consensus review involving both reviewers. If consensus cannot be reached, a third party reviewer will make the final determination.

Diagnosis of Kawasaki disease will be based on the American Heart Association Diagnosis and the Centers for Disease Control and Prevention guidelines.[^13^](#_ENREF_13)^,30^ Our primary diagnosis for Kawasaki disease will include patients meeting the following criteria:

- ≥4 principal features and a fever (≥38.0˚C) persisting ≥5 days *or* fever until the date of administration of IVIG if given before the 5^th^ day of fever
- Evidence of < 4 principal features and coronary artery disease (aneurysm or dilation) by echocardiography or coronary angiography *and* fever (≥38.0˚C) of any duration.

Possible Kawasaki disease will be defined as evidence of 2 or 3 principal features and ≥ 5 days of fever. A large proportion of our study population will be under the age of 1 year, and some principal clinical features may frequently be absent in young infants.[^13^](#_ENREF_13) A sensitivity analysis will be conducted including possible Kawasaki disease in the case definition.

For cases of Kawasaki disease without a prior PCV vaccination history, the immunization record will be sought from the child’s primary care provider to verify that the patient was not vaccinated with a PCV vaccine or correct the absence of the vaccination record.

The positive predictive value of the Kawasaki disease ICD-9 and ICD-10 code to identify confirmed cases will be determined for all the cases captured by the definition, stratified by Data Partner, PCV13 vaccine dose, and timing relative to PCV13 vaccination. We will evaluate the positive predictive values of the ICD-9 and ICD-10 code based algorithms for Kawasaki disease separately and combined together.

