“Incomplete” or “atypical” Kawasaki disease can also be diagnosed in patients presenting with fever for ≥5 days and <4 of the clinical features, if coronary artery disease is diagnosed using echocardiography or coronary angiography.[^13^](#_ENREF_13) The diagnosis of incomplete Kawasaki disease is more common in infants <6 months of age, and these patients are more likely to develop coronary artery abnormalities as compared with infants between 6 and 12 months of age.[^13-15^](#_ENREF_13) In general, physicians are encouraged to consider a diagnosis of Kawasaki disease in febrile patients with fewer clinical features of Kawasaki disease in the absence of cardiac complications for prompt treatment to reduce the risk of coronary artery aneurysms.[^16^](#_ENREF_16) If left untreated, approximately 25% of patients develop coronary artery aneurysms which may lead to additional cardiac complications including myocardial infarction, sudden death or ischemic heart disease.[^13^](#_ENREF_13)^,^[^17^](#_ENREF_17)^,^[^18^](#_ENREF_18) Intravenous immunoglobulin administration has been identified as a successful treatment in reducing cardiac complications in Kawasaki disease patients if promptly administered within 10 days of illness onset. Aspirin is also used in the treatment of Kawasaki disease for the anti-inflammatory and anti-platelet effects.

Numerous factors have been shown to affect the incidence of Kawasaki disease in the United States. The illness presents most commonly in Americans of Asian and Pacific Island descent, with an incidence of 32.5/100,000 in children <5 years of age compared to 9.1/100,000 for non-Hispanic whites of the same age group.[^13^](#_ENREF_13)^,^[^19^](#_ENREF_19) In addition, Kawasaki disease is age-dependent, with 80% of cases occurring before age 5 years, and a peak incidence at 13-24 months of age.[^20^](#_ENREF_20) Many studies have reported increased incidence of Kawasaki disease in males, with male to female ratios ranging from 1.5-1.7 : 1.[^4^](#_ENREF_4)^,^[^7^](#_ENREF_7)^,^[^19^](#_ENREF_19)^,^[^21^](#_ENREF_21)^,^[^22^](#_ENREF_22) Seasonality is also believed to have some impact on incidence.[^19^](#_ENREF_19)

[figure not shown]

Figure 2. “Number of cases in the National Inpatient Sample (NIS) data presented by patients’ age. The number of cases peaks at patients 1 to 2 years of age, followed by patients <1 year and 2 to 3 years of age, and then the number continues to decrease towards older age.”[^23^](#_ENREF_23)

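### Primary case definition: with coronary disease and short fever not ended by early IVIG, a child with 0-3 principal features is a case but one with 4-5 is not

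*Protocol*

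**What the plan says.** Protocol IV.F (Medical Chart Review) gives two routes to a primary case and one lesser category.

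- Route 1: "≥4 principal features and a fever (≥38.0˚C) persisting ≥5 days", or alternatively "fever until the date of administration of IVIG if given before the 5^th^ day of fever".
- Route 2 (coronary): "Evidence of < 4 principal features and coronary artery disease (aneurysm or dilation) by echocardiography or coronary angiography", together with "fever (≥38.0˚C) of any duration". There is no lower limit on the number of features.
- Lesser category, used only in a sensitivity analysis: "Possible Kawasaki disease will be defined as evidence of 2 or 3 principal features and ≥ 5 days of fever".

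The background (II.C, Kawasaki Disease) describes incomplete disease differently, as patients "presenting with fever for ≥5 days and <4 of the clinical features, if coronary artery disease is diagnosed using echocardiography or coronary angiography". There the coronary route carries a 5-day fever minimum; in IV.F it does not.

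IV.F also says of the first 10 double-reviewed charts: "This initial round of case classification will enable refinement of the classification rules".

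**The concern.** A case definition should be monotone: holding everything else fixed, one more principal feature should not move a child from case to non-case. Route 2 treats coronary disease with any fever as sufficient even when no principal feature is present. Nothing in the protocol explains why the same child with 4 or 5 features should then be excluded.

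The rule defines the outcome of the primary self-controlled analysis and of the cohort analysis. It also fixes the numerator of the positive predictive value (PPV), which is the second objective and decides whether the automated-code analysis is reported (threshold 0.8, IV.E.8). Confirmed cases are few, so an accidental hole is worth closing even if it is small.

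**Working it through.** **Logical check.** There is no plan figure to reproduce. Take a child with coronary aneurysm or dilation and apply the IV.F rules literally to every feature count.

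| Fever | 0-3 features | 4-5 features |
| --- | --- | --- |
| (a) 5 days or more | primary (route 2) | primary (route 1) |
| (b) under 5 days, lasting until IVIG given before day 5 | primary (route 2) | primary (route 1, IVIG clause) |
| (c) under 5 days, not lasting until such IVIG | primary (route 2) | **not a case** |

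In row (c), the child with 4-5 features fails route 1 on fever and route 2 on the feature count. The possible category fails on both, since it needs 2 or 3 features and at least 5 days of fever, so the sensitivity analysis does not recover the child. The inversion is confined to row (c).

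**Where it comes from.** Replace the fever condition of route 2 by the 5-day minimum in II.C and repeat:

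- Row (a): all feature counts are cases.
- Row (b): only 4-5 features are cases.
- Row (c): none are cases.

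No row is inverted. The upper limit on features is harmless in that form, because any child with 4 or more features and 5 days of fever enters by route 1. The hole appears only when the limit is combined with fever of any duration.

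**Two ways to make the rule monotone.**

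- Drop the upper limit in route 2: the 4- and 5-feature cells of row (c) become primary cases, and no other cell with coronary disease changes.
- Restore the 5-day minimum in route 2: the 0-3 feature cells of rows (b) and (c) stop being cases, unless the IVIG clause is carried over to route 2 for row (b).

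**Size.** Inputs from IV.E.6: 3,388,104 doses; 8.7 coded diagnoses per 100,000 person-years; 40% ultimately confirmed; 28-day windows.

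- Confirmed rate: 8.7 × 0.4 = 3.48 per 100,000 person-years.
- Person-years per window: 3,388,104 × 28 / 365.25 ≈ 259,700.
- Expected confirmed cases per window at the background rate: 259,700 × 3.48 / 100,000 ≈ 9.04.
- Both windows: 9.04 × 2 ≈ 18.1 at a relative risk of 1; 9.04 × 2.9 ≈ 26.2 at 1.9.

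The protocol gives no frequency for row (c) with 4-5 features. Assuming 1% to 4% of confirmed cases:

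- Relative risk 1: 0.01 × 18.1 ≈ 0.2 to 0.04 × 18.1 ≈ 0.7 cases.
- Relative risk 1.9: 0.01 × 26.2 ≈ 0.3 to 0.04 × 26.2 ≈ 1.0 cases.

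**The case against.** The best defence is that the limit of fewer than 4 features is not a slip: it matches the protocol's own account of incomplete disease in II.C. What departs from II.C is the fever wording in IV.F. This stands. It means the documents do not show which of the two phrases was meant to give way.

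Other points on that side, and what remains of them:

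- A reader might infer that every child with 4-5 features, coronary disease and fever under 5 days is rejected. That is too strong. The IVIG clause of route 1 confirms those whose fever lasted until IVIG given before day 5 (row (b)).
- A reader might infer that the excluded children are certainly true cases. The documents do not settle this. These children miss the fever minimum of route 1, and their status is a clinical judgement. What the text does show is that the protocol accepts the same child with fewer features.
- A reader might infer a biased relative risk. Nothing supports that. Classification is blinded to vaccination status and the same rule applies in risk and control windows, so any loss should be non-differential.
- A reader might infer that nothing planned could retain such a child. The automated-code analysis would, since it does not use the chart criteria, but it is exploratory and is reported only if the PPV reaches 0.8. Rule refinement after the first 10 charts could also close the gap, but those charts may contain no such child. Double review does not help either, because two reviewers applying the text literally would agree.

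**Conclusion.** The concern holds in a narrow form. With coronary aneurysm or dilation and fever under 5 days that did not last until IVIG given before day 5, the stated rule makes 0-3 features a primary case and 4-5 features no case at all, not even a possible one. This is an inconsistency in a rule that is written down, not a detail left for later, and it follows from the text without any assumption.

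The practical effect is probably small. At an assumed frequency of 1-4% it is at most about one confirmed window case, with a slight lowering of the PPV numerator. The expected case counts rest on the power section's dose count, background rate and 40% confirmation, and the frequency itself has no source in the protocol. The cost is a few lost cases and an illogical outcome definition; no bias in the relative risk is demonstrated.

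**What to change.** Reconcile the coronary route in IV.F with the description in II.C so that additional principal features can never turn a confirmed case into a non-case, and state explicitly how coronary disease with 4 or more features and short fever is classified.

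If fever of any duration is kept in the coronary route, delete its upper limit on features. For example, the second criterion could cover any child who does not meet the first but has fever of at least 38.0°C of any duration and coronary aneurysm or dilation on imaging, whatever the number of principal features. This keeps every child whom the operative definition now confirms. If the 5-day minimum in II.C was intended instead, the sponsor should say so and state whether the IVIG clause also applies to the coronary route.

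Settle the wording before chart classification begins, not during the refinement step. The cost is one line in the case definition and the matching line of the classification rules. The definition already depends on features, fever and coronary imaging, so no further data are needed.

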In 2000, FDA licensed the first pneumococcal conjugate vaccine, 7-valent pneumococcal vaccine (PCV7) (Prevnar; Wyeth), for use in infants and young children. PCV7 protected against strains of *Streptococcus pneumoniae* that most commonly caused illness among children in the U.S. Subsequently, inclusion of PCV7 in the recommended children immunization program resulted in decreased rates of invasive pneumococcal disease.[^8^](#_ENREF_8) The CDC reported that rates of PCV7-type invasive pneumococcal disease in children under 5 years of age dropped from 80 cases per 100,000 to less than 1 case per 100,000 following the implementation of the PCV7 vaccine.[^9^](#_ENREF_9) FDA licensed a second vaccine, PCV13 on February 24^th^, 2010 to protect against 6 additional serotypes that accounted for much of the invasive pneumococcal disease in young children not covered by the PCV7 vaccine.[^10^](#_ENREF_10) The Advisory Committee on Immunization Practices (ACIP) recommended PCV13 for use as a 4-dose vaccination series, administered at 2, 4, 6 and 12-15 months of age, similar to the PCV7 vaccine recommendations. Full implementation of the transition from PCV7 to PCV13 came into effect in March 2010 with supplies of PCV13 available to the public sector that month as shown in Figure 1.[^11^](#_ENREF_11) By July 2010, Pfizer reported that >90% of its private shipments of pneumococcal conjugate vaccines were for PCV13.[^11^](#_ENREF_11) Children previously vaccinated with PCV7 finished their remaining vaccinations with PCV13. A dose of PCV13 was recommended by ACIP for children 14-59 months of age who had completed the 4-dose vaccination series with PCV7, and children with specified underlying medical conditions receive a 5^th^ dose until 71 months of age.[^10^](#_ENREF_10)

[figure not shown]

Figure 1. “Pneumococcal conjugate vaccine doses administered to children aged 0 through 59 months, by vaccine type and week --- Immunization Information System sentinel sites, United States, March 7--August 21, 2010.” [^11^](#_ENREF_11)

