## Exposure Codes

- PCV13 vaccination will be identified by the CPT code 90670 and the NDC codes 00005197101, 00005197102, 00005197104, 00005197105.
- PCV 7 vaccination will be identified by the NDC codes 00005197049, 00005197050, 00005197067, 54569511700.
- Unspecified PCV vaccine will be identified by HCPCS codes G0009, S0195 and the CPT code 90669. (The latter code is technically for PCV7, but we will treat it as “unspecified” PCV in order to guard against possible misclassification of PCV13 as PCV7.)

Unspecified PCV vaccine prior to February 24, 2010 will be assumed to be PCV7 and after August 2010 will be assumed to be PCV13 based on the date of approval for PCV13 and the fact that by July 2010, Pfizer reported that >90% of its private shipments of pneumococcal conjugate vaccines were for PCV13.[^11^](#_ENREF_11) Information related to unspecified PCV vaccines received between Feb 24 and Aug 31, 2010, will not be included in analyses. Data on all vaccinations occurring within the first two years of life will also be captured.

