### Overview of hypothesis-testing analyses

A challenge in studying PCV13 and Kawasaki disease will be the confounding effect of age, as both vaccination and the risk of Kawasaki disease are age-dependent. To confront this challenge, we will use both a *self-controlled risk interval (SCRI)*[*^26^*](#_ENREF_26)*^,^*[*^27^*](#_ENREF_27) and a *cohort* design. A major advantage of the former, which we are pre-specifying as the primary method, is that it inherently controls for all fixed (non-time-varying) potential confounders such as gender, race/ethnicity, and chronic predisposing conditions, by virtue of each subject serving as his/her own control. Another advantage of the SCRI design is that it uses only exposed cases, thus minimizing potential misclassification bias due to incomplete data on vaccine exposure. A possible disadvantage is that adjustment for time-varying confounders such as age must be made explicitly, and estimation of the age effect may introduce error. The cohort design is likely to have higher statistical power than the self-controlled design, due to the relatively large amount of historical and concurrent unexposed data involved in the generation of expected counts. However, its ability to control for time-invariant confounding is not as good as that of the self-controlled approach. If there are differences among racial/ethnic groups in vaccine coverage and timing, an important potential confounder in the cohort design will be race/ethnicity. The point estimates are also subject to bias from misclassification of exposure if some vaccinations are not recorded in the claims data and not captured during the chart review process.

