### Cohort Poisson Regression Analysis

The second design that we will use is a cohort design with unconditional Poisson regression, including the exposed person-time from the time of licensure of PCV13 (February 2010) to the most up-to-date data, and unexposed person-time for the entire cohort from the year 2008 to the most up-to-date data. The following covariates will be included in versions of the Poisson regression model before settling on the most parsimonious and explanatory model: vaccination risk window (yes/no), age in weeks modeled as a continuous variable, sex, and calendar year as a continuous variable, and Data Partner. It is not feasible to include race/ethnicity as a covariate in this analysis as that information is not widely available in the Sentinel data. Exposed person-time will be the 1-28 days after PCV13 vaccination, while unexposed time will be the time outside of the 7 days before through the 42 days after vaccination with either PCV13 or PCV7. (We exclude the 7 days prior to vaccination from unexposed time in order to control for the healthy vaccinee effect and similar effects that could result from dependency of vaccination on one’s health condition in the week prior.) We will include unexposed person-time from children who are not vaccinated with PCV7 or PCV13 but have at least one documented healthcare visit. A polynomial risk function will be used to refine estimates of background rates by week of age during the first 1.5 years of life. We will systematically try at least linear, quadratic, cubic, fourth-order, and fifth-order functions, without exposure in the model (to blind ourselves to the effect of vaccination), and select the function to include in the final model based on the log-likelihood ratio, p-value, Akaike information criterion (AIC), and biologic plausibility. If we cannot find a well-fitting polynomial function, we will try splines instead.

Dose PCV13 Kawasaki disease

unexposed exposed unexposed

Figure 5. Cohort design to evaluate the incidence rate ratios comparing rates in the exposed and unexposed intervals

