# Dataset Creation

We will use the Sentinel distributed Common Data Model (MSCDM), which allows Data Partners to maintain control over patient-level data. Data Partners extract and output data into eight files of standard format. The files relevant for the present study are: enrollment, demographic, encounter, procedure, diagnosis and dispensing.

Sentinel programmers will provide Data Partners with programs to be run on the patient-level files. The programs will produce aggregate data on vaccinations and Kawasaki disease organized in strata defined by variables such as week of vaccination, type of vaccine, dose number, age, Data Partner, and sex, with counts of patients, vaccine doses and Kawasaki disease in particular strata. Data Partners will return the aggregate data for analysis at Harvard, using Sentinel’s secure file transport methods.

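### Missing vaccination records are recovered only for cases; if those doses are used in the cohort analysis, as the protocol implies, its rate ratio is pushed modestly above 1 under the null.

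*Protocol*

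**What the plan says.** - **Correction for cases.** Medical Chart Review: "For cases of Kawasaki disease without a prior PCV vaccination history, the immunization record will be sought from the" primary care provider, either to confirm that the child was unvaccinated "or correct the absence of the vaccination record". This applies only to Kawasaki disease cases with no PCV history.
- **Exposure for everyone.** Exposure Codes defines exposure by billing and drug codes: "PCV13 vaccination will be identified by the CPT code 90670 and the NDC codes" listed there, with parallel lists for PCV7 and unspecified PCV.
- **Denominators.** Dataset Creation: "The programs will produce aggregate data on vaccinations and Kawasaki disease organized in strata defined by variables such as week of vaccination" and other variables. No step checks or corrects the records of non-cases.
- **Cohort definitions.** Cohort Poisson Regression Analysis: "Exposed person-time will be the 1-28 days after PCV13 vaccination, while unexposed time will be the time outside of the 7 days before" vaccination through 42 days after it. Children with no PCV record count as unexposed: "We will include unexposed person-time from children who are not vaccinated with PCV7 or PCV13 but have at least one documented healthcare visit".
- **The protocol's own caveat.** The Overview of hypothesis-testing analyses says that cohort estimates may be biased "if some vaccinations are not recorded in the claims data and not captured during the chart review process".

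**The concern.** The caveat in the Overview treats a dose found during chart review as a problem solved. That is right only if the same correction reaches the denominator, and here it reaches cases alone. Take a vaccinated child with no PCV code who develops Kawasaki disease:

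- Onset in days 1-28 after PCV13: after correction the case joins the exposed count.
- Onset in days -7 to 0 or 29-42: the case leaves the unexposed count and is dropped.
- Onset at any other time: the case stays unexposed.

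The risk-window and excluded days of that child, and of all similar children without the disease, remain in unexposed person-time. The first two movements both raise the rate ratio. Uncorrected, the missing records would leave the null value at 1.

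The cohort design is the second hypothesis-testing design, and the protocol expects it to have more power than the primary one. Evaluation of Elevated Risks starts follow-up work after a significant excess in any analysis. The bias also points the same way as the signal under study, and a larger sample would not shrink it.

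**Working it through.** The protocol gives no cohort rate ratio, cohort power or share of missing records, so there is no figure of its own to reproduce. The check uses expected counts with a true rate ratio of 1.

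**Inputs from the protocol.** Each dose has 28 exposed days (1-28) and 22 excluded days (7 before, day 0, and 29-42), 50 in all. Doses are "administered at 2, 4, 6 and 12-15 months of age", so these spans do not overlap on schedule. Follow-up runs to at most 23.99 months.

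**Assumptions.** v = share vaccinated and recorded, m = share vaccinated but unrecorded, u = share truly unvaccinated, s = share of missing records found for cases. Follow-up is T = 548 days with 3.5 doses per child, all PCV13, and a flat background rate. Per vaccinated child:

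- exposed days E = 28 × 3.5 = 98
- excluded days X = 22 × 3.5 = 77
- unexposed days U = 548 − 98 − 77 = 373

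**Formula.**

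RR = [(v + m·s)/v] ÷ {[v·U + u·T + m·(T − s·(E + X))] / [v·U + u·T + m·T]}

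**Example: m = 5%, u = 5%, v = 90%, s = 1.**

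- Exposed part: 0.95/0.90 = 1.0556.
- Unexposed cases: 0.90×373 + 0.05×548 + 0.05×(548 − 175) = 381.75.
- Unexposed time: 0.90×373 + 0.05×548 + 0.05×548 = 390.50.
- Ratio: 381.75/390.50 = 0.9776.
- RR = 1.0556/0.9776 = 1.080.

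| v, m, u | none found (s=0) | half found (s=0.5) | all found (s=1) |
|---|---|---|---|
| 0.95, 0.02, 0.03 | 1.000 | 1.015 | 1.031 |
| 0.90, 0.05, 0.05 | 1.000 | 1.039 | 1.080 |
| 0.85, 0.10, 0.05 | 1.000 | 1.083 | 1.169 |

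**Sensitivity.** With four doses, 730 days and 5% unvaccinated, the values are 1.029, 1.075 and 1.159 with all found, and 1.014, 1.037 and 1.078 with half found. Across 3 to 4 doses and 1.2 to 1.9 years, the all-found ranges are 1.03-1.04, 1.07-1.10 and 1.15-1.21. For the secondary 1-42 day analysis the formula gives the same values, because (v + m·s)/v and the 50-day total per dose are unchanged.

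**Age adjustment.** A Poisson model with a cubic in age, fitted to expected counts under an assumed age curve with 5% unvaccinated, gave 1.09 and 1.20 at m = 5% and 10% with all found, 1.04 and 1.09 with half found, and 1.00 with none. Adjusting for age does not remove the bias.

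**Scale against sampling error.** Statistical power gives 3,388,104 doses and 8.7 per 100,000 person-years: 3,388,104 × 28/365.25 × 8.7/100,000 = 22.6 expected risk-window cases under the null. At the confirmed rate of 3.5 the figure is 9.1. The exposed count alone implies 95% limits of about ×/÷ exp(1.96/√22.6) = 1.51, or exp(1.96/√9.1) = 1.92. At m = 5% the correction adds 22.6 × 0.05/0.90 = 1.3 exposed cases, or 0.5 confirmed. At 10% it adds 22.6 × 0.10/0.85 = 2.7, or 1.1 confirmed.

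**Cost of claims-only classification.** With a true rate ratio of 2 and s = 0, the estimate is 2/[1 + m·E/(v·U + u·T + m·T)]. At 5% this is 2/(1 + 4.9/390.5) = 1.98; at 10% it is 2/(1 + 9.8/399.25) = 1.95.

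**The case against.** The strongest reply is that the harmful step is inferred. Medical Chart Review does not say which analysis uses a corrected record, the cohort section mentions no chart-corrected exposure, and Exposure Codes relies on codes alone. This detail might be settled in an analysis plan that is not at hand. That limits confidence. It does not dispose of the point, because the Overview's caveat concerns the cohort estimate and makes sense only if doses found in chart review are used there.

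The size can also be challenged, and most of that challenge stands. The all-found figures are upper values for each assumed share. The power section assumes 80% chart retrieval. Review is capped at 200 cases, with first call for those in self-controlled windows, and a case with no coded dose has no such window in claims. A shift of 1.03 to 1.08 lies well inside the sampling error shown above. One qualification: the dose counts come from four Data Partners and six will take part, so precision may improve while the bias does not.

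A reader might infer that every corrected case moves into the exposed count. Only onsets in days 1-28 do, which is 98/548 or about 18% of follow-up in the illustration. A reader might also infer that the primary result is compromised. It is not: the self-controlled analysis uses cases only, and a recovered case can fall in either window.

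**Conclusion.** The concern holds in conditional form. If recovered doses enter the cohort model, as the Overview implies, cases and person-time are classified from different sources and the null rate ratio is biased upward. The direction is certain whenever some vaccinated children lack a record and some of those cases are corrected. The size rests on assumed unrecorded shares of 2% to 10%: from about 1.01 (2%, half found) to about 1.17 (10%, all found) in the closed form.

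The documents do not support the stronger conclusion that the cohort analysis will produce a false signal. Reassignment is not stated outright, the unrecorded share is unknown, and the likely shift is small against the cohort's imprecision. Because the design affected is not the primary one, this should be fixed rather than must be fixed. Confidence is medium.

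**What to change.** 1. In Cohort Poisson Regression Analysis and Medical Chart Review, state that the main cohort analyses (1-28 and 1-42 days) classify both cases and person-time by claims codes only.
2. Amend the Overview to say that correcting records for cases alone does not remove cohort misclassification and can bias the estimate upward.
3. Use provider-corrected dates in the self-controlled analyses.
4. In the cohort, use them only in a labelled sensitivity analysis that also reassigns the estimated share of uncoded person-time. For the 1-28 day analysis, days 1-28 go to exposed time, and days -7 to 0 and 29-42 to excluded time. For the 1-42 day analysis, days 1-42 go to exposed time and days -7 to 0 to excluded time. Taking the days out of unexposed time without adding the risk-window part to exposed time would leave the exposed rate inflated by 0.95/0.90 = 1.056 at 5%.
5. Report that analysis over a range of assumed shares, since any estimate from the few cases without a PCV history will be weak.

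The cost is a few sentences and one further cohort run, with no new records. The main cohort estimate keeps the milder bias toward 1 from unrecorded doses when a true effect exists: about 1.98 or 1.95 in place of 2 at 5% or 10% unrecorded. The rule should be fixed before exposure-linked results are seen.
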